Both treatments share some common, non-specific effects, while they differ on their specific effects. The basic strategy in family psychoeducation attempts to reduce the impact of environmental stress on biologically vulnerable individuals by promoting communication within the family, increasing coping skills and improving problem-solving abilities [30]. These outcomes are expected to be produced by: a) providing information about the disorder, which should also decrease the pathogenic impact of ‘false myths’ concerning the illness; b) the provision of coping strategies to manage crises; c) the implementation of a more comfortable environment where support is provided by peers and professionals. Within this framework, non-specific effects include emotional support, empathic listening, and the implementation of therapeutic optimism. Specific effects, expected to influence therapeutic outcome, are thought to be the consequence of specific and well-defined treatment strategies. In the FPP, the specific effects are thought to be the consequences of improved problem-solving, better coping and tolerance to stress, and improved social skills acquired by the intervention. In the GT, the specific effects are essentially the reduction of shame and sense of guilt obtained by explicitly talking about situational problems related to the disorder, and the modelization on the non-judgmental, empathic and supportive behavior of the therapist.

For both the FPP and GT, participation in the meetings by each family member who has expressed willingness to participate will be recorded. A family will be considered adherent to the psychoeducation treatment when at least one member of the family has participated in 70% of the meetings (n = 12 out of 18). The rate of family attendance will be considered as a confounding variable in the evaluation of outcome. Percentage of drop-out by type of psychoeducation treatment (families who have not participated in three successive meetings and have not attended at least 70% of meetings overall) will be considered as an independent measure of applicability of the method (FPP or GT).

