A number of related, secondary outcomes will be assessed: the occurrence of psychotic symptoms, according to the Brief Psychiatric Rating Scale (BPRS) and the Positive and Negative Syndrome Scale (PANSS); the general level of psychopathology, according to the Health of the Nation Outcome Scales (HoNOS); changes in social functioning, according to the Personal and Social Performance scale (PSP), and in the quality of life, as evaluated on the WHO-Quality of Life-Short form (WHOQOL-Bref); changes in the patient’s overall clinical status, as measured by the Clinical Global Impression (CGI); changes in the dosage of the prescribed drugs, as a reflection of changes in adherence to therapy; and, finally, changes in the frequency of relapse and readmission. Italian validated versions of the scales will be used. The BARS and the Family Questionnaire (see below) were translated for this study.

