### Expressed emotion in the patient’s family

The concept of expressed emotion (EE) was developed to describe the emotional environment and the attitude of caregivers towards a relative affected by a disorder. The Camberwell Family Interview (CFI) is the standard reference for this type of study [48], and measures the amount of critical comments (CCs), hostility (H), or emotional over-involvement (EOI) expressed by a close relative when talking about a mentally or physically ill family member. High EE consistently predicts the risk of relapse for patients with schizophrenia [49,50], but the CFI is time-consuming, and requires detailed training of the assessors. The Family Questionnaire (FQ) is a brief self-report questionnaire aimed at measuring expressed emotion on a four-point Likert scale, from 0 (never/rarely) to 4 (often/always) [51]. The FQ provides two subscale scores: critical comments (CC) and emotional over-involvement (EOI). Scores of 24 or higher on the CC subscale or 28 or higher on the EOI subscale define the occurrence of EE in the family. The FQ was proved to relate to EE rating by the CFI. FQ scores will be analyzed both as a confounding variable to explore the role of EE in the effectiveness of psychoeducation, and as an outcome measure to evaluate whether FPP or GT can improve EE levels in the patient’s family.

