### Medication

The study is open about the psychopharmacological treatment, with no treatment restrictions. On the basis of the study’s sample size, we expect equal distribution of type (classical versus atypical antipsychotics), dose, rate of non-adherence to medication, and prescription of other psychopharmacological treatment (antidepressants, mood stabilizers, benzodiazepines) in both treatment groups. Since the type and medication dose are potential confounders, they will be controlled.

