### Ethical considerations

The FPP is not expected to produce relevant somatic side effects but it can produce unwanted or unforeseen effects, such as an increase in the intra-family level of conflict. To maximize safety for the patients, before randomization each patient will be evaluated on his or her risk of unwanted or unforeseen effects attributable to exposure to the FPP.

The therapists involved in the administration of the FPP and GT will be monitored to minimize any improper method of administration of the protocol of treatment; assessors will also be trained and monitored to avoid dispersion of information, thus violating the guaranteed criterion of good faith in case of patients’ disclosing sensitive information. Data recording and storage will comply with the privacy law in force, and informed consent for information recording will be obtained from each patient.

Participation in the study is voluntary and written informed consent is obtained. Before enrollment, participants will receive both verbal and written assurance that they can withdraw from the trial any time, with no consequence for their continued treatment. Patients unable to give informed consent in an appropriate way or who refuse to participate in the study will not be enrolled.

The Training Center is committed to monitoring the quality of assessment and of the administration of the FPP procedures, on a three-month basis.

A paradoxical, unintended effect of greater adherence to pharmacotherapy is the potential increase of the somatic side effects of the prescribed drugs. Indeed, there is some indirect evidence that this can actually occur [66]. To limit this paradoxical effect, patients will be closely monitored for side effects and somatic conditions on a three-month basis or as needed. It is expected that, following improvement in the response to the therapy as a result of greater adherence to pharmacotherapy, the therapist will decrease dosage of the prescribed drugs. This specific change will be checked at assessment and a reduction of dosage of the prescribed drugs and of poly-pharmacotherapy is among the secondary outcomes of the study.

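### Family attendance arises after randomisation but is to be treated as a confounder; any between-arm effect adjusted for it is not the intention-to-treat effect and can be biased in either direction

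*Protocol article*

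**What the plan says.** **Attendance.** The Planned interventions section of the protocol article says: "The rate of family attendance will be considered as a confounding variable in the evaluation of outcome". The statement is unqualified and does not say which analysis it applies to. The next sentence turns attendance-based drop-out, by type of programme, into a result: it "will be considered as an independent measure of applicability of the method (FPP or GT").

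**Attendance threshold.** In the same section a family counts as adherent to the programme when "at least one member of the family has participated in 70% of the meetings (n = 12 out of 18"). The drop-out definition combines missing three meetings in a row with falling short of 70% overall.

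**Planned analyses.** Data management and analysis compares the primary outcome with a two-tailed test of proportions, without covariates, and applies intention-to-treat as far as possible. It adds a multiple logistic regression whose confounders are named as sex, age, severity of the disorder and cluster. Assessment and outcome measures adds a continuous adherence index, intended for covariance analyses that examine confounders of the primary outcome, but names no covariates for it.

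**Dose and expressed emotion.** Medication says: "Since the type and medication dose are potential confounders, they will be controlled". Dose change is also an outcome: Assessment and outcome measures lists "changes in the dosage of the prescribed drugs, as a reflection of changes in adherence to therapy", and Ethical considerations says "a reduction of dosage of the prescribed drugs and of poly-pharmacotherapy is among the secondary outcomes of the study". The section on expressed emotion says "FQ scores will be analyzed both as a confounding variable to explore the role of EE in the effectiveness of psychoeducation", and also "as an outcome measure to evaluate whether FPP or GT can improve EE levels in the patient’s family". Neither covariate statement names the visit whose value would be used. Table 3 shows the FQ and the dosage record scale (DOTES) collected at T0.

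**The concern.** A confounder of a treatment comparison is a cause of the outcome that is also associated with treatment for reasons other than treatment itself. Randomisation removes that association except by chance. Attendance cannot play this part, because it comes into being only after allocation, at sessions whose content differs by arm.

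Adjusting the FPP-versus-GT effect for attendance does two things:

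- It removes whatever part of the effect works by keeping families in the programme.
- If family motivation drives both attendance and drug adherence, comparing families with equal attendance links arm to motivation. A difference can then appear where none exists, or a real one can shrink.

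At stake is the reading of the adjusted results. The Discussion presents the ability to control for confounders and covariates as an advantage of the trial. An analyst who follows the sentence in Planned interventions could report an adjusted effect that disagrees with the intention-to-treat result, and readers might prefer it because it is adjusted.

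**Working it through.** **1. The threshold (the plan's own figure on this point).** 0.70 × 18 = 12.6 meetings, whereas the plan gives 12. 12/18 = 66.7%; 13/18 = 72.2%. A family that attends exactly 12 meetings is adherent by the count but below 70% under the drop-out rule. If it also missed three in a row, it is classed both ways.

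**2. Which analyses could contain attendance.**

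| Analysis | Covariates named | Attendance named? |
|---|---|---|
| Two-tailed test of proportions (primary) | none | no |
| Multiple logistic regression | sex, age, severity, cluster | no |
| Covariance analysis of the continuous index | not listed | open |

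The statement on attendance therefore disagrees with the logistic covariate list, and the covariance analysis is the obvious place left for it to act.

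**3. Can attendance differ by arm?** The documents give no attendance figures. The protocol compares attendance-based drop-out by programme, so it allows for a difference.

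**4. Illustrative size.** From the documents: 18 meetings; GT adherence 53% (1 − 0.47, from Sample size and power); N = 340; two-sided 0.05. Assumed: everything else. With T = 1 for FPP and U a standard normal family motivation:

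- meetings attended ~ Binomial(18, p), logit p = 1.0 + a·T + 0.8·U; A = meetings/18
- logit P(adherent) = c + d·T + b·(A − 0.7) + g·U, with c set to give 53% adherence in GT

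Logistic models were fitted with and without A to 400,000 simulated patients. Odds ratios are for adherence, FPP versus GT.

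| Scenario | a, b, g, d | Attendance GT / FPP | OR without A | OR with A |
|---|---|---|---|---|
| No effect, FPP attends more | 0.6, 0, 1, 0 | 71% / 81% | 1.00 | 0.64 |
| No effect, FPP attends less | −0.6, 0, 1, 0 | 71% / 59% | 1.01 | 1.65 |
| No effect, equal attendance | 0, 0, 1, 0 | 71% / 71% | 1.00 | 1.00 |
| Effect partly through attendance | 0.6, 3, 0.5, 0.6 | 71% / 81% | 2.17 | 1.43 |
| Effect wholly through attendance | 1.2, 5, 0, 0 | 71% / 88% | 2.23 | 1.00 |

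In the fourth row the risk difference falls from 0.18 to 0.07. With a direct effect and equal attendance (a = 0, b = 0, g = 1, d = 1.2), the risk difference is 0.225 both ways. The odds ratio still moves, from 2.73 to 3.12, because odds ratios change when a predictor of outcome is added; this is not confounding.

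**5. False-positive rate with no true effect**, N = 340, 2,000 runs, b = 0, g = 1:

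| a | Without A | With A |
|---|---|---|
| 0 (equal attendance) | 4.6% | 4.5% |
| 0.3 (about 71% / 76%) | 4.2% | 16% |
| 0.6 (71% / 81%) | 3.6% | 44% |

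**6. Sensitivity to the form of the covariate.** If attendance enters as yes/no (60% FPP, 75% GT) and motivation acts on both attendance and adherence with log-odds 0.7 to 1.5 per SD, the adjusted odds ratio under no effect is 1.07 to 1.21. With the rates reversed it is 0.83 to 0.93. The direction is the same and the size much smaller. The protocol speaks of the rate, which is the form used in steps 4 and 5.

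**The case against.** The strongest reply is that the trial's main result is untouched. The primary test has no covariates, and the logistic model names four, none of them attendance. A reader might infer that the plan breaks the randomised comparison; the documents do not support that. This part of the reply stands and confines the point to adjusted analyses outside those two.

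A reader might also infer that dose and expressed emotion are to be adjusted for at follow-up, so that outcomes serve as covariates. The text does not say so. The sentence in Medication before "Since the type and medication dose are potential confounders, they will be controlled" expects both groups to be alike in drug type, dose and rate of non-adherence. Non-adherence is the primary outcome and is expected to differ after treatment (25.5% against 47%), so that sentence reads most naturally as baseline. A baseline covariate and a later change as outcome do not conflict. For the FQ, exploring the role of expressed emotion in effectiveness may mean effect modification by the T0 score. Which visit's value enters a model is also commonly left to the analysis plan. For these two variables only a clarification is warranted.

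The size of bias is assumed, and under no effect there is none when the arms attend equally. That stands too: attendance can bias the estimate; it need not.

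The threshold slip touches only a process measure, and the listed primary analyses do not use it. It is minor.

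What the reply does not answer is the statement on attendance itself. It has no baseline value, so no choice of visit rescues it, and it is a stated rule rather than a detail left open.

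**Conclusion.** The point holds in limited form. Attendance is wrongly labelled a confounder, and the label disagrees with the logistic covariate list. A between-arm effect adjusted for it would not be the intention-to-treat effect and could err either way if attendance differs by arm. The unadjusted primary test and the logistic model as listed are not affected.

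The size cannot be taken from the documents. Under the assumptions shown, a null effect became an odds ratio anywhere from 0.64 to 1.65 with the attendance rate as covariate, and stayed at 1.00 when attendance was equal. These figures show that the bias can matter; they are not a forecast.

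That attendance arises after allocation and has no baseline value needs no simulation. For dose and the FQ, the documents establish only that the visit is unstated. The mismatch between 70% and 12 of 18 is a separate, minor inconsistency.

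**What to change.** 1. In Planned interventions, delete the statement that attendance is a confounder. Say instead that it will be reported by arm and will not enter any model that estimates the FPP-versus-GT effect. If an effect among attending families is wanted, make it a supplementary complier-average analysis that uses allocation as the instrument, with its assumptions stated.
2. Reconcile that section with the covariate list in Data management and analysis, and name the covariates for the covariance analysis of the continuous index.
3. As clarification in Medication and in the expressed-emotion section, state that drug type, dose and FQ enter any adjusted model only at their t0 values, since changes in dose and in FQ are also outcomes.
4. Make the attendance threshold agree with itself in both the adherence and the drop-out definitions: either 13 of 18 (72.2%) with 70% kept, or 12 of 18 with 70% restated as two thirds.

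The cost is wording only. Table 3 already has the FQ and the dosage record at T0, attendance is already recorded, and no sample-size figure changes.

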### Assessment and outcome measures

Assessment is aimed at investigating the clinical and functional status of the patients and evaluating the main effects of treatment on the primary and secondary outcome measures (Table 3). The primary outcome is the patient’s adherence to pharmacotherapy, intended as the continuous use of the primary prescribed drug. Even if patients with psychosis are generally under poly-pharmacotherapy, only adherence to the most important drug (the one expected to produce the main therapeutic effect), as indicated by the enrolling unit, will be monitored during the study. Adherence will be checked by a triple method of assessment: patient’s self-report on the Medication Adherence Rating Scale (MARS), patient’s replies to the four-query interview of the Brief Adherence Rating Scale (BARS), and measurement of blood levels of the prescribed drug. Data will be analyzed using two indicators of adherence:

1. a dichotomic index, where non-adherence is the lack of adherence to the treatment in 30% or more of the monthly evaluation on the self-report or the interview (since replies on both measures might not coincide);

2. a continuous index based on the scale - self-report or interview - which could be the most reliable by comparison with the measurement of blood levels of the primary prescribed drug, to apply statistical analyses of covariance and verify the impact of confounding variables on the primary outcome.

**Table 3 T3:** Timing of assessments of endpoints for efficacy and safety

	**T0**	**T1**	**T2**	**T3**
Background information (age, sex, diagnosis, and so on)	X			
Clinical Global Impressions	X	X	X	X
Brief Psychiatric Rating Scale (BPRS)	X	X	X	X
Positive And Negative Syndrome Scale (PANSS)	X	X	X	X
Social Performance Scale	X	X	X	X
Health of the Nation Outcome Scales (HoNOS)	X	X	X	X
World Health Organization Quality Of Life (WHOQoL)	X	X	X	X
The Family Questionnaire	X	X	X	X
Medication Adherence Rating Scale	X	X	X	X
Brief Adherence Rating Scale	X	X	X	X
Dosage Record and Treatment Emergent Symptoms Scale (DOTES)	X	X	X	X
Sheenan-Suicidality Tracking Scale (S-STS)	X	X	X	X
Modified Overt Aggression Scale (MOAS) 1.0	X	X	X	X
Blood sample for assessing of the blood level of the prescribed drug	X	X	X	X
Assessment of blinding				X

A number of related, secondary outcomes will be assessed: the occurrence of psychotic symptoms, according to the Brief Psychiatric Rating Scale (BPRS) and the Positive and Negative Syndrome Scale (PANSS); the general level of psychopathology, according to the Health of the Nation Outcome Scales (HoNOS); changes in social functioning, according to the Personal and Social Performance scale (PSP), and in the quality of life, as evaluated on the WHO-Quality of Life-Short form (WHOQOL-Bref); changes in the patient’s overall clinical status, as measured by the Clinical Global Impression (CGI); changes in the dosage of the prescribed drugs, as a reflection of changes in adherence to therapy; and, finally, changes in the frequency of relapse and readmission. Italian validated versions of the scales will be used. The BARS and the Family Questionnaire (see below) were translated for this study.

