**Methods:**

340 patients diagnosed with schizophrenia and related disorders according to standardized criteria from 10 participating units distributed throughout the Italian National Health System (NHS), will be enrolled with 1:1 allocation by the method of blocks of randomized permutations. Patients will be reassessed at 6, 12 and 18 months after start of treatment (duration: 6 months).

The primary objective is to evaluate changes in adherence to pharmacotherapy after psychoeducation. Adherence will be assessed at three-month intervals by measuring blood levels of the primary prescribed drug using high pressure liquid chromatography, and via the Medication Adherence Questionnaire and a modified version of the Adherence Interview. Secondary objectives are changes in the frequency of relapse and readmission, as the main indicator of the course of the disorder.

Enrolled patients will be allocated to the FPP (yes/no) randomly, 1:1, in a procedure controlled by the coordinating unit; codes will be masked until the conclusion of the protocol (or the occurrence of a severe negative event). The raters will be blind to treatment allocation and will be tested for blinding after treatment completion. Intention-to-treat will be applied in considering the primary and secondary outcomes. Multiple imputations will be applied to integrate the missing data. The study started recruitment in February 2013; the total duration of the study is 27 months.

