### Timing

In the first three months of the study, the Coordination Center and all directors of the participating units will check the organization of the study, the assessment methodology, the training of the assessors and their inter-rater agreement.

As far as the investigational trial is concerned, we foresee three months for the enrollment of the patients; six months for the subsequent exposition to the FPP of the patients allocated to treatment (the exposed group), or same-length GT for the unexposed group; there will be subsequent six-month and twelve-month follow-ups to verify whether the immediate benefit of FPP, if any, is maintained after the conclusion of the FPP treatment. Patients will be evaluated at entry (t0), at the conclusion of the treatment (both exposed and unexposed) (t1), after six months of follow-up (t2) and after twelve months of follow-up (t3). The final report will be made within six months of the conclusion of the study, but initial reports will be prepared six months after the start (see Figure 1).

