### Assessment tools

The MARS is a ten-item yes/no self-report instrument. Total scores vary from 0 (low likelihood of medication adherence) to 10 (high likelihood). From this scale, we used the five items specifically referring to the taking or not of the medication [31,32]. Therefore in our MARS version, total scores vary from 0 (low likelihood of medication adherence) to 5 (high likelihood).

The BARS is a brief, pencil-paper, clinician-administered adherence assessment instrument [33]. The BARS consists of four items: three questions and an overall visual analog rating scale to assess the percentage of doses taken by the patient in the past month (0% to 100%). The visual analog scale rating serves as a final adherence determination. The three questions inquire about patients’ knowledge of their own medication regimen and episodes of missed medication taking, and include: number of prescribed doses per day (question 1); number of days, over the past month, the patient did not take the prescribed doses (question 2); and number of days, over the past month, the patient took less than the prescribed doses (question 3). A higher score on the BARS corresponds to better adherence.

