### Follow-up assessment

The FPP has a six-month duration, so patients will be assessed at entry (t0), at the end of the FPP (t1), at the six-month follow-up (t2), and at the twelve-month follow-up (t3), for secondary outcome measures. Adherence will be monitored at t0, t1, t2, and t3, via self-reports, interviews and measured blood levels of the primary prescribed drug.

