### Sample size and power

Sample size for the identification of the expected difference in the primary outcome (adherence to pharmacotherapy) was based on known evidence: prevalence of non-adherence to pharmacotherapy in patients already in contact with a psychiatric service is around 40 to 50%, median = 47% [11,12]; effect size of psychosocial treatment on various outcomes, including relapse, readmission and adherence to pharmacotherapy is 0.48 of the standard deviation (SD), with 95% CI= 0.10 to 0.85 [16]. We expect that our intervention could produce a change in the prevalence of non-adherence to pharmacotherapy in the exposed group with an effect size of 0.45 SD [11,12]. After performing a test of difference between proportions we determined that a sample of 78 participants per group would be needed to achieve 80% power to detect a difference with h = 0.45 (medium effect size) in the measures of adherence to pharmacotherapy, at a two-sided significance level of 0.05 and allocation ratio of 1:1.

Cohen’s h effect size for the difference of proportions is calculated on the formula:

$$h=2^{*}\arcsin\;p1-2^{*}\arcsin\;p2$$

where p1 and p2 are the proportions of adherent patients in the exposed group 1 and the non-exposed group 2, respectively [59]. The Cohen’s h measures the same effect size interval as the Cohen’s d but is based on differences by proportion rather than by continuous variables [59].

Cohen’s h = 0.45 implies that at the estimated power (= 80%) we can observe a 25.5% rate of non-adherence to pharmacotherapy in the exposed group as opposed to a 47% rate in the unexposed group. In this case, risk reduction is 0.215, corresponding to a number needed to treat (NNT) = 5. Since we do not know the exact proportion of non-adherence, here are the different starting p1 and related maximum p2 detectable:

p1: 0.65 0.60 0.55 0.50 0.45 0.40 0.35 0.30 0.25

p2: 0.43 0.38 0.33 0.28 0.24 0.20 0.16 0.12 0.09

Since this a multisite study, the clusterized nature of the data has to be controlled since it has an impact on an unequal variance by center, which requires a correction of the sample according to the formula:

$$\mathrm{DE}=1+\left(m-1\right)\times r$$

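### The yes/no primary adherence index counts monthly evaluations that are not scheduled, so its rule has several readings with different rates and power

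*Protocol article*

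**What the plan says.** The protocol article gives three frequencies for the same outcome.

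- **Monthly.** Assessment and outcome measures defines the dichotomous index: "non-adherence is the lack of adherence to the treatment in 30% or more of the monthly evaluation on the self-report or the interview". The self-report is MARS and the interview is BARS.
- **Six-monthly.** Follow-up assessment: "Adherence will be monitored at t0, t1, t2, and t3, via self-reports, interviews and measured blood levels of the primary prescribed drug". Table 3 marks MARS, BARS and the blood sample at the same four points. Timing and the abstract place the visits after entry at 6, 12 and 18 months.
- **Three-monthly.** Abstract, Methods: "Adherence will be assessed at three-month intervals by measuring blood levels of the primary prescribed drug", with the questionnaire and the interview in the same sentence.

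The only monthly element that can be delivered is a recall period. Under Assessment tools, the BARS visual analogue scale is there to "assess the percentage of doses taken by the patient in the past month (0% to 100" per cent), and it settles the patient's adherence status. The trial's MARS is five yes/no items scored 0 to 5, with no cut-off stated.

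Sample size and power compares two single proportions of non-adherence, 47% and 25.5%. Data management and analysis tests the primary outcome as a difference in proportions and names no visit.

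**The concern.** A rule of 30% or more of the evaluations needs a known number of evaluations, and the article gives three incompatible ones. This goes beyond detail left to an analysis plan, because the published sections contradict each other on the denominator of the primary endpoint.

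The readings measure different things. A count over t1 to t3 is a cumulative status over 18 months. A count that includes t0 puts a pre-treatment value into the outcome. A past-month dose percentage is a status at one visit. They give different control rates and respond differently if the benefit fades after treatment ends. The Timing section treats that as an open question, since the follow-ups are there to see whether any benefit is maintained. If the reading is not fixed beforehand, the choice could decide the primary result.

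**Working it through.** **1. The plan's own figure.** Inputs from Sample size and power: 47% vs 25.5%, h = 0.45, two-sided alpha 0.05, power 80%, 1:1.

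- h = 2·arcsin√0.47 − 2·arcsin√0.255 = 0.452.
- n = 2·((1.960 + 0.842)/0.45)² = 77.5, so 78 per group, as stated.

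The arithmetic is sound. The difficulty lies in what the 47% and 25.5% refer to.

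**2. What 30% or more means on each schedule.**

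- t1 to t3: 1 of 3 (33%).
- t0 to t3: 1 of 4 is 25% and falls short, so 2 of 4.
- Three-monthly to 18 months: 1 of 6 is 17%, so 2 of 6.
- Doses missed in the past month: a per-visit status, with no counting of visits.

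**3. Rates and power under the counting rules.** Assumptions: 47% (control) and 25.5% (FPP) at each post-baseline visit, and 47% in both arms at t0 because it precedes treatment. The documents give no within-patient correlation, so a latent (probit) correlation ρ from 0 to 0.9 is assumed. Visit j is non-adherent when √ρ·U + √(1−ρ)·Eⱼ < Φ⁻¹(pⱼ), with U shared across the patient's visits. Power = Φ(h·√(78/2) − 1.96), before clustering and dropout.

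Independent visits (ρ = 0) by hand:

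- 1 of 3, control: 1 − 0.53³ = 0.851.
- 1 of 3, FPP, constant effect: 1 − 0.745³ = 0.587.
- 1 of 3, FPP, effect at t1 only: 1 − 0.745 × 0.53² = 0.791.
- 2 of 4, control: 1 − 0.53⁴ − 4 × 0.47 × 0.53³ = 0.641.
- 2 of 4, FPP: none bad 0.53 × 0.745³ = 0.2192; exactly one bad 0.47 × 0.745³ + 3 × 0.53 × 0.255 × 0.745² = 0.4194; so 1 − 0.2192 − 0.4194 = 0.361.

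For ρ > 0 the same probabilities are averaged over U. The h values come from unrounded rates.

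| Reading | ρ | Control | FPP | h | Power, 78 per group |
|---|---|---|---|---|---|
| 1 of 3, constant effect | 0 | 85% | 59% | 0.605 | 97% |
| | 0.5 | 72% | 47% | 0.520 | 90% |
| | 0.9 | 58% | 34% | 0.473 | 84% |
| 1 of 3, effect at t1 only | 0 | 85% | 79% | 0.158 | 17% |
| | 0.5 | 72% | 67% | 0.121 | 11% |
| | 0.9 | 58% | 54% | 0.069 | 6% |
| 2 of 4 with t0, constant effect after t0 | 0 | 64% | 36% | 0.567 | 94% |
| | 0.5 | 56% | 36% | 0.412 | 73% |
| | 0.9 | 51% | 33% | 0.363 | 62% |

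For comparison, t1 alone at 47% vs 25.5% has h = 0.452 and power Φ(0.452 × 6.245 − 1.96) = 81%, whatever happens later.

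**4. The either-instrument rule.** If MARS and BARS each flagged 47% of patients independently, 1 − 0.53² = 72% would be non-adherent at a single visit. In practice they will overlap, so this is only an illustration. It shows that 47% need not be the rate for an index that fires on either instrument.

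**The case against.** The strongest reply is that the monthly evaluation is the BARS recall month. A patient would then be non-adherent when 30% or more of the doses in that month were missed. This needs no monthly visits, is a status at one visit, and is compatible with a 47% prevalence. The reply stands as a possible reading, and the example under the fix uses it. It does not settle the matter. The text does not choose this reading, it applies the 30% rule to MARS as well, where five yes/no items give no percentage of doses, and it leaves the analysis visit open.

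A second reply is that no power is lost. For one of three with a constant effect that is right: power is 84% to 97%. The protocol also says that the exact rate is unknown and tabulates starting rates from 0.25 to 0.65, although the higher cumulative control rates (72%, 85%) lie outside that table.

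A third reply is that an analysis plan not shown may fix the reading, and that the statistical units receive neutral group codes. Both limit the risk of a choice driven by results. Neither removes the contradiction between the sections as published.

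**Conclusion.** The point holds: the primary dichotomous index cannot be computed as written on the schedule given, and the sections that set the assessment interval disagree. Under the stated assumptions, one of three gives about 58% to 85% against 34% to 59%, and two of four including t0 gives about 51% to 64% against 33% to 36%. At 78 per group, power runs from 6% to 17% (one of three, effect at t1 only) up to 84% to 97% (one of three, constant effect), with two of four between 62% and 94%. The ranges rest on assumed correlations and an assumed per-visit contrast.

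A reader might infer three stronger things that the documents do not support:

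- That the rule, taken literally, means any one bad visit. That requires leaving t0 out; over the four scheduled points it takes two.
- That the index cannot match the 47%. The past-month-doses reading could.
- That the trial is underpowered. Power falls below 80% only under particular combinations: an effect that does not last, or t0 counted with high visit correlation.

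**What to change.** Define the index on evaluations that the schedule delivers, exclude t0 from the outcome, and name one primary visit. One workable version takes t1, with non-adherence as 30% or more of doses missed in the past month on the BARS visual analogue rating, and t2 and t3 as secondary. If MARS stays in the either-instrument rule, state its cut-off; otherwise report it as supportive. Remove the reference to monthly evaluations and make the abstract, Assessment and outcome measures with Table 3, and Follow-up assessment give the same interval. Then confirm in Sample size and power that the 47% refers to the index so defined, or re-derive the control rate.

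The cost is wording in the protocol and analysis plan, with no new data. The downside is that the either-instrument rule must be given an explicit MARS cut-off or be narrowed to one instrument.
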